### Data analyses

Demographic, clinical and prognostic characteristics of the study participants will be collected and described in detail. The number of participants with missing data for each variable of interest will be provided along with an analysis to check for selective missingness. Average follow up time will be determined for each model. Reports on adjusted and unadjusted values with confounders will be presented along with 95 percent confidence intervals. Confounders that change beta coefficients more than 10% will be reported.

### Effect evaluation

Data will be analyzed by the intention to treat principle. Propensity score techniques will be used to address potential selection bias [60]. The propensity score is a one-dimensional summary measure that is directly related to the predicted probability that a subject with specific baseline characteristics is included in the intervention group (relative to the control group) [60]. Propensity scores are derived as the fitted linear predictor values from a logistic regression model with treatment (per case management model versus usual care) as the outcome variable. All variables on which groups differ at baseline are included as covariates. Depending on the mismatch of the intervention and control group on these propensity scores we will use 1-to-1 matching, stratified (quintile) matching or choose to include the propensity score as a confounder in the regression models for treatment effects [61].

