Reviews and meta-analyses of case management have yielded inconsistent results on clinical outcomes such as caregiver burden and depression and on economic outcomes [28-31]. Furthermore, only short term effects on caregiver satisfaction were found [32]. Only one meta-analysis including 15 studies found that risk of institutionalization of dementia patients was reduced by multicomponent interventions aimed at caregivers [28]. Based on this meta-analysis, clinicians are advised to tailor interventions according to the specific needs of the individual caregivers and care receivers [28]. Several reviews have indicated that further research should distinguish subpopulations that could benefit from case management [28-30].

In the Netherlands, patients and caregivers are highly satisfied with case management [33]. However, various models of case management are implemented, differing with respect to how services are delivered and by whom, the training provided to its staff and the means of financing. It is unknown whether there are also differences in clinical and cost-effectiveness between these case management models compared with usual care. In the COMPAS study, two different case management models are studied, that is the linkage model and the intensive case management/joint agency model. These models will be compared with usual care and with each other (description in Table 1). These case managements models were chosen based on their emerging prominence in Dutch healthcare for a number of years. The objective of this study is to identify differences in clinical, process and cost outcomes for people with dementia and informal caregivers between the two case management models and the usual care model. Furthermore, the aim is to identify facilitators and barriers in the implementation of the two case management models. This process evaluation focusses on which aspects are successful and their pitfalls.

**Table 1 T1:** Comparison of case management models and care as usual

**Characteristics of different models**	**Linkage Model**	**Intensive Case management/joint agency model**	**Care as usual**
Central point for registration of cognitively impaired	New clients are referred by GP or health specialist to the central registration point	New clients are referred by GP or health specialist to the Multidisciplinary team at central registration point	No
Delivery of services	Independent services and networks	Mainly offered by one organization	Various networks

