Possibility to diagnose dementia	By GP or referral to e.g. memory clinic or elderly care physician of mental health care service	By GP or by Multidisciplinary team after referral to central registration point	By GP or referral to memory clinic or elderly care physician of mental health care service
Case manager/dementia nurse	Yes	Yes	nurse present, incidentally
Social psychiatric nurse	No	No	Possible
Multidisciplinary team	External team that case managers can consult as per required	Case manager, elderly care physicians, neuropsychologist, neurologist, geriatrician, psychiatrist, dementia consultant all work within the same organisation as the case managers	No

Our first hypothesis is that in the two case management models the persons with dementia will have less behaviour and mood problems than persons receiving usual care and informal caregivers experience better mental health compared to usual care. Furthermore, we expect a delay in nursing home admission for persons with dementia versus usual care because care needs are better monitored and followed up by services that cooperate within a chain of care. Additionally, an exploratory hypothesis is whether the intensive care/joint agency model is associated with fewer behavioural problems and better follow up care compared to the linkage model, as the services that are part of one organisation may generate more efficiency.

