### Quality of care outcome measures

Quality of care at the micro level of the care receivers is measured by:

(1) 12 indicators on treatment, education, support, and safety (translated and back-translated) from Vickrey asked to the informal caregiver, such as care plan developed, behavioural problems discussed, and non-pharmacological treatments [43];

(2) 10 Indicators from the problems and needs questionnaire, developed by the Dutch Alzheimer Association in conjunction with the Netherlands Institute for Primary Care Research (NIVEL), asked to the informal caregivers [27].

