At the regional level, confounding by socio-economic differences may limit the internal validity of the comparisons. This will be corrected for by using socio-economic characteristics of the patients (e.g. education), demographic factors (e.g. age and marital status) and by checking for clustering at the regional level in the multilevel analysis. The case management models may differ in their development (some regions started case management recently while others already exist for ten years), referral modality, the case loads of case managers and their funding, causing within and across case-management model type heterogeneity, which could have an effect on the care received by the person with dementia and their carer. A description of each model will help identify differences. The risk of selection bias potentially occurs at the patient level. Firstly, there may be confounding by indication and confounding by severity of cognitive impairments, as the likelihood of referral to case-management by a general practitioner may depend on patient characteristics, such as severity of dementia. Potential confounders include demographics like age, gender, education of patients and caregivers, time in case management, dementia severity (MMSE, dementia-type and caregiver burden (Sense of Competence questionnaire [51]). Baseline characteristics of the patients in the three intervention groups will be compared and post-hoc matching techniques and stratification will be used when necessary [39]. In a secondary analysis, semi-structured interviews with a random sample of general practitioners will be performed to identify reasons for case management referral and, thus, to identify potential selection bias. Secondly, in our opinion, there is a risk of only recruiting dementia caregivers who experience relatively less burden, limiting the external validity of the study. A non-responder analysis will be completed to identify this source of potential bias and matching techniques will be used to correct for variables such as severity of cognitive impairments (MMSE), time since diagnosis and age and health of the person with dementia and caregiver.

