Attrition bias will also be analysed as an increase in severity of the disease (and therefore burden of disease). This will probably predict drop-out, leading to ‘survival’ of a relatively healthy population for the intention to treat analysis. The solution is to rigorously retrieve information on drop-outs, for example in cases where the caregiver or care receiver has died or was institutionalized. Proxy measurements will be used when the care receiver refuses or is not able to completely answer the questions in order to avoid missing data. The caregiver will act as the proxy. Proxy measurements will be used for the EQ-5D, CANE and QoL-AD. As case management is growing quickly in the Netherlands, recruiting unexposed client dyads may be a serious problem. If it appears to be impossible to recruit enough controls, then only the different case management groups will be compared against each other. A more general problem is recruiting enough people to participate, and subsequently to maintain them, in the study. As this is a burdened population that is also frequently recruited for other studies, recruiting dyads for this study is challenging and attrition rates may be high. We plan to address this in two ways. First, we must explain to participants the importance of this research as it identifies who benefits from case management and who may not and it will endeavour to determine the most efficient model. Secondly, we made every effort to avoid burdening the caregivers with unnecessary interviews or questions. An important limitation might be a relatively low participation rate that fuels confounding by indication and hinders adequate stratified analyses. As all potential participants were approached at the full time spectrum since diagnosis (except for an expected institutionalization within 6 months), an important assumption is, that the effectiveness of case management is constant over time. However, a review by Pimouguet et al. [29] found an early time effect on case management under a year and then less of an effect later on. We will handle this by using time in case management as a covariate to correct for differences between subjects in the groups. The generalizability of the results for clinicians and policy makers will largely depend on achieving the sample size required, the homogeneity of the population samples and our ability to adequately correct for potential confounders and effect modifiers in the statistical analyses. Despite the limitations addressed here, we expect that this study will provide important information on dementia case management models in The Netherlands for policy makers, health care providers, patients and informal caregivers.

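### The propensity score takes its covariates from observed baseline differences, with no guard against consequences of case management or omitted prognostic factors, and no score is defined for linkage versus intensive case management

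*Protocol article*

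**What the plan says.** All references are to the protocol article.

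- **Covariate rule (Effect evaluation).** "All variables on which groups differ at baseline are included as covariates". The article does not define what counts as differing, forces no variable in and keeps none out.
- **Scores fitted (Effect evaluation).** The score comes from a "logistic regression model with treatment (per case management model versus usual care) as the outcome variable".
- **Comparisons (Background).** "These models will be compared with usual care and with each other". The second of these is exploratory: "an exploratory hypothesis is whether the intensive care/joint agency model is associated with fewer behavioural problems and better follow up care compared to the linkage". The Discussion adds that, if too few controls can be recruited, "then only the different case management groups will be compared against each other".
- **Timing of exposure (Procedure; Discussion).** Everyone currently in case management is screened, at any time since diagnosis. Study baseline in those arms therefore comes after case management has begun.
- **Named confounders (Discussion).** The list includes time in case management and "caregiver burden (Sense of Competence questionnaire"). Secondary clinical outcomes and Table 2 list that same questionnaire as a secondary caregiver outcome.
- **Other adjustment.** Data analyses plans adjusted and unadjusted results and will report confounders that move a coefficient by more than 10%. The Discussion plans correction for socio-economic and demographic factors, a covariate for time in case management, and matching or stratification of the three groups after the fact if needed.

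**The concern.** In a non-randomised comparison the propensity score is the main protection against selection bias, so what enters it matters. Choosing covariates by observed group difference can fail in two directions.

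First, it can admit consequences of exposure. A variable that case management has already changed is more likely to differ between groups, and so more likely to be selected. Adjusting for it removes part of the effect. A variable that is close to a marker of exposure damages overlap instead.

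Second, it can leave out a prognostic factor with a real but modest imbalance, and the confounding it carries stays in.

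Separately, a score fitted only against usual care does not serve the linkage-versus-intensive contrast. The Discussion itself expects the models to differ in referral route, maturity and caseload.

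**Working it through.** **The plan's own figure.** From Sample size: SDs 13.7 and 20.3, within-subject correlation 0.5, difference 5.2, one-sided alpha 0.05, power 80%.
- SD of change = SD × √(2 × (1 − 0.5)) = SD, so the change SDs stay 13.7 and 20.3.
- Root-mean-square SD = √((13.7² + 20.3²)/2) = 17.3.
- The Satterthwaite t-test needs 138 per group, and power at 140 is 80.5%. The stated 140 is reproduced, and 140/0.80 = 175. This figure is not in dispute. It supplies the SD, the target difference and the group size used below.

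**Omitted prognostic factors.** Assumptions, none from the article: differing means two-sided p<0.05; the true imbalance is 0.20 SD; the covariate-outcome correlation is 0.3 to 0.5.
- SE of the standardised difference at 175 per group = √(2/175) = 0.107, and 0.20/0.107 = 1.87, p about 0.06.
- Chance that the factor is not selected:

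| True imbalance (SD) | 140 per group | 175 per group |
|---|---|---|
| 0.10 | 0.87 | 0.85 |
| 0.20 | 0.61 | 0.54 |
| 0.30 | 0.29 | 0.20 |
| 0.40 | 0.08 | 0.04 |

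- Bias when an observed 0.20 SD imbalance is left out = correlation × 0.20 × 17.3. This is 1.04 points at correlation 0.3 and 1.73 at 0.5, or 20% and 33% of 5.2.
- Simulating the whole rule (true imbalance 0.20 SD, correlation 0.5, 175 per group, 4,000 samples) gives an average bias of 0.58 points, 11% of 5.2. Always adjusting gives 0.00. The average is lower because the factor is sometimes selected and because, when it is missed, the observed imbalance tends to be smaller than 0.20 SD.

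**Consequences of exposure.** Assumptions: a true total effect of −5.2, part of it already present at baseline; baseline-to-follow-up correlation 0.5; 175 per group; 1,000 samples per row.

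| Effect already present at baseline | Chance baseline NPI is selected | Estimate adjusted for a score containing it |
|---|---|---|
| 1.0 | 10% | −4.7 |
| 2.6 | 26% | −3.9 |
| 4.0 | 59% | −3.2 |

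The estimates agree with −5.2 + 0.5 × (effect already present): −4.7, −3.9, −3.2. The larger the prior effect, the more likely the rule is to adjust it away. This is a loss only if the target is the total effect of case management, and the article states no target in these terms.

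**Time in case management.** Under Usual care, participants as a rule have no case manager. If this variable entered a score against usual care, it would separate the groups almost completely.

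**Linkage versus intensive.** Effect evaluation fits scores only "with treatment (per case management model versus usual care) as the outcome variable". If the fallback is used, there is no usual care group to fit either score against.

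**The case against.** The case on the other side has real content.

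- **Other adjustment is planned.** The 10% criterion in Data analyses would flag a covariate that moves the estimate by 20% to 33%, and the Discussion commits to correcting for age, education and marital status. This stands as partial mitigation. However, the 10% criterion governs reporting, and none of this text is tied to the propensity score or said to override its covariate rule.
- **Quality-of-care indicators.** A reader might infer that items "such as care plan developed, behavioural problems discussed, and non-pharmacological treatments" will enter the score, because they are measured at baseline and should differ. The article does not say so. Table 2 lists confounders separately from quality of care, and the Discussion's list does not name the indicators. What stands is that the rule, read literally, does not exclude them. The Sense of Competence score and time in case management are different: the article itself names both as confounders.
- **Baseline NPI and GHQ-12.** A reader might infer that these too must stay out, since Primary clinical outcome measures expects case management to affect behaviour and caregiver stress. That does not follow. The sample size is built on change scores, and if the target is change after enrolment, adjusting for them is defensible.
- **Linkage versus intensive.** A reader might infer that this contrast is unadjusted. It is not: matching, stratification and a time-in-case-management covariate are mentioned. It is also exploratory, and the fallback is conditional. What is missing is a specified score.
- **Article format.** Exact model specification can be left to a fuller plan. The covariate rule and the restriction to usual care, however, are stated choices that a fuller plan would inherit.

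**Conclusion.** The point holds in bounded form. The stated rule has no safeguard against admitting consequences of prior case management, and the article's own confounder list contains a secondary outcome and a variable absent in usual care. The rule can also leave out imbalanced prognostic factors: about 54% of the time for a true 0.20 SD imbalance at 175 per group, if differing means p<0.05.

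The bias is 1.0 to 1.7 NPI points when an observed imbalance of that size is left out. It is about 0.6 points averaged over the rule at correlation 0.5. Both figures are before any recovery through the other planned adjustments. A reader might take 1.7 points as the expected bias, but it is near a worst case: it needs the p<0.05 reading, an imbalance just below the threshold, a correlation of 0.5 and no other adjustment. Imbalances, correlations and prior effects are all assumed.

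The linkage-versus-intensive contrast lacks a score. Its exploratory status limits the weight of this unless the recruitment fallback is used. Overall this should be changed, but it does not by itself invalidate the study.

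**What to change.** Replace the covariate rule with a pre-specified list entered whatever the observed difference, and reconcile it with the Discussion's list of confounders:

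- **Patient:** age, sex, education, living situation, dementia type, comorbidity, MMSE, ADL, time since diagnosis.
- **Caregiver:** age, education, relation to the patient.
- **Baseline NPI and GHQ-12:** state that the target is change after enrolment, include them on that basis, and add a sensitivity analysis without them because they may already reflect earlier case management.
- **Keep out of the main score:** quality-of-care indicators and the Sense of Competence score.
- **Time in case management:** leave it out of scores against usual care and keep it for linkage versus intensive.
- **Linkage versus intensive:** fit a separate score for this contrast.
- **Balance:** judge it by standardised differences.

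The cost is wording and analysis time. The variables are already collected (Table 2; date of diagnosis under Procedure). The downside is a few more covariates, one extra score and one sensitivity analysis. The sample size does not change.

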### Economic evaluation

A societal perspective is used in this economic evaluation. Missing data will be imputed using multiple imputation. As patient/caregiver-level cost data have a highly skewed distribution, bootstrapping will be performed to estimate Approximate Bootstrap Confidence (ABC) intervals around cost differences [62,63]. Incremental cost-effectiveness ratios (ICERs) will be calculated by dividing the difference in total costs between the case management models and usual care by the difference in clinical effects. Non-parametric bootstrapping will also be used to estimate the uncertainty surrounding the ICERs (5000 replications). The bootstrapped cost-effect pairs will be plotted on a cost-effectiveness plane (CE plane) [64] and used to estimate cost-effectiveness acceptability curves (CEA curves). CEA curves illustrate the probability that the intervention is cost-effective in comparison with the control treatment for a range of ceiling ratios. The ceiling ratio is defined as the societal willingness to pay in order to gain one unit of effect [65].

### Process evaluation

For the process evaluation, semi-structured interviews with key figures will be typed out verbatim and analysed by two researchers independently from each other. Codes will be used to analyse the text fragments using the method of constant comparison of data extracts for each code [66]. The software Atlas-ti will be used for this purpose. The findings will be summarized in matrices, with facilitators and barriers at different levels (micro, meso, macro) and in different phases of the implementation (preparation, implementation and continuation). Descriptive analyses will be performed regarding the data on characteristics of case management (questionnaires from the case manager).

## Discussion

This study is a two year, prospective, observational, controlled, cohort study among persons with dementia and their primary informal caregiver receiving different types of case management or usual care. The study will be carried out in several regions of the Netherlands and will be accompanied by a qualitative process evaluation. Comparing two widely advocated and implemented dementia case management care models with usual care, will provide valuable information on process, clinical and cost outcomes. The extensive collection of outcomes measured, together with the naturalistic design of the cohort study and the length of follow-up are unique features of this study. This study will provide relevant information on the effect of different case management models on behaviour and quality of life in persons with dementia, on general health and burden of caregivers, and on costs and conditions for successful implementation of case management. This information endeavours to identify strengths and weaknesses of each model and may help in future policy and decision making. While various models of case management for dementia are implemented in multiple regions in the Netherlands [33], this appears to be one of the first studies to compare different case management models with usual care. As this is an observational study and treatment assignment is not randomized, bias is more likely to occur. Various forms of bias must be systematically addressed like in any prospective cohort study [67]. This includes various forms of bias from a regional level, a case management level and at an individual level.

At the regional level, confounding by socio-economic differences may limit the internal validity of the comparisons. This will be corrected for by using socio-economic characteristics of the patients (e.g. education), demographic factors (e.g. age and marital status) and by checking for clustering at the regional level in the multilevel analysis. The case management models may differ in their development (some regions started case management recently while others already exist for ten years), referral modality, the case loads of case managers and their funding, causing within and across case-management model type heterogeneity, which could have an effect on the care received by the person with dementia and their carer. A description of each model will help identify differences. The risk of selection bias potentially occurs at the patient level. Firstly, there may be confounding by indication and confounding by severity of cognitive impairments, as the likelihood of referral to case-management by a general practitioner may depend on patient characteristics, such as severity of dementia. Potential confounders include demographics like age, gender, education of patients and caregivers, time in case management, dementia severity (MMSE, dementia-type and caregiver burden (Sense of Competence questionnaire [51]). Baseline characteristics of the patients in the three intervention groups will be compared and post-hoc matching techniques and stratification will be used when necessary [39]. In a secondary analysis, semi-structured interviews with a random sample of general practitioners will be performed to identify reasons for case management referral and, thus, to identify potential selection bias. Secondly, in our opinion, there is a risk of only recruiting dementia caregivers who experience relatively less burden, limiting the external validity of the study. A non-responder analysis will be completed to identify this source of potential bias and matching techniques will be used to correct for variables such as severity of cognitive impairments (MMSE), time since diagnosis and age and health of the person with dementia and caregiver.

Attrition bias will also be analysed as an increase in severity of the disease (and therefore burden of disease). This will probably predict drop-out, leading to ‘survival’ of a relatively healthy population for the intention to treat analysis. The solution is to rigorously retrieve information on drop-outs, for example in cases where the caregiver or care receiver has died or was institutionalized. Proxy measurements will be used when the care receiver refuses or is not able to completely answer the questions in order to avoid missing data. The caregiver will act as the proxy. Proxy measurements will be used for the EQ-5D, CANE and QoL-AD. As case management is growing quickly in the Netherlands, recruiting unexposed client dyads may be a serious problem. If it appears to be impossible to recruit enough controls, then only the different case management groups will be compared against each other. A more general problem is recruiting enough people to participate, and subsequently to maintain them, in the study. As this is a burdened population that is also frequently recruited for other studies, recruiting dyads for this study is challenging and attrition rates may be high. We plan to address this in two ways. First, we must explain to participants the importance of this research as it identifies who benefits from case management and who may not and it will endeavour to determine the most efficient model. Secondly, we made every effort to avoid burdening the caregivers with unnecessary interviews or questions. An important limitation might be a relatively low participation rate that fuels confounding by indication and hinders adequate stratified analyses. As all potential participants were approached at the full time spectrum since diagnosis (except for an expected institutionalization within 6 months), an important assumption is, that the effectiveness of case management is constant over time. However, a review by Pimouguet et al. [29] found an early time effect on case management under a year and then less of an effect later on. We will handle this by using time in case management as a covariate to correct for differences between subjects in the groups. The generalizability of the results for clinicians and policy makers will largely depend on achieving the sample size required, the homogeneity of the population samples and our ability to adequately correct for potential confounders and effect modifiers in the statistical analyses. Despite the limitations addressed here, we expect that this study will provide important information on dementia case management models in The Netherlands for policy makers, health care providers, patients and informal caregivers.

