### Sample size

The sample sizes for the controlled cohort study are calculated based on the primary outcome measures NPI [37] and the GHQ-12 [38]. Based on Callahan et al. [42], who investigated the effect of collaborative care, the estimated change between baseline and follow-up after 12 months on the NPI was −2.5 (SD 13.7) in the intervention group and 2.7 (SD 20.3) in the control group, resulting in a difference of −5.2. The standard deviations reported are the averages for the two time points. Standard deviations of baseline and follow-up scores were assumed equal when calculating the required sample size. The NPI has moderate to high test - retest reliability scores therefore we assumed a within-subject correlation of 0.5 to estimate the standard deviation for the difference scores based on the standard deviations of the baseline and follow-up [11]. A sample size of 140 participants per group is considered sufficient (80% power) to detect a difference of 5.2 in change scores between the groups. This calculation was based on a two group Satterthwaite *t*-test at a one sided significance of α = 0.05. To allow for a drop-out rate of 20% (including patients who withdraw or die in the course of the study), 175 (140/0.80 = 175) participants per group will be recruited.

Based on a study by Dias et al., the difference in GHQ baseline and follow-up at six months was −1.4 (SD 2.8) for the caregiver intervention group and 0.8 (SD 3.4) in the control group [59]. The GHQ has moderate to high test-retest reliability scores. A within-subject correlation of 0.6 when estimating the standard deviation of the difference scores was used. Using a two group Satterthwaite *t*-test with a onesided significance level of α = 0.05, an initial sample size of 21 in each group was estimated to have 80% power to detect a difference in means of −2.2 on the GHQ. A dropout rate for caregivers was assumed at 20% which resulted in a final sample size of at least 26 caregivers per group [59].

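### The recruitment fallback removes the usual-care comparison altogether, leaving the first hypothesis untested on both primary outcomes, although a shortfall of controls does not require this

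*Protocol article*

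**What the plan says.** The Discussion notes that case management is spreading quickly in the Netherlands and that finding unexposed dyads may be difficult. It then states: "If it appears to be impossible to recruit enough controls, then only the different case management groups will be compared against each other".

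The Background ranks the comparisons. The comparison with usual care comes first: "Our first hypothesis is that in the two case management models the persons with dementia will have less behaviour and mood problems" than those under usual care, and caregivers are expected to have better mental health. The comparison between models ranks lower: "an exploratory hypothesis is whether the intensive care/joint agency model is associated with fewer behavioural problems" than the linkage model.

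The Sample size section is built only on intervention-versus-control differences. For the NPI: "A sample size of 140 participants per group is considered sufficient (80% power) to detect a difference of 5.2" in change scores, tested "at a one sided significance of α = 0.05". For the GHQ-12: "an initial sample size of 21 in each group was estimated to have 80% power" for a difference of 2.2, also one-sided at 5%. After 20% drop-out the recruitment targets are 175 and at least 26 per group. No effect size or power is given for linkage versus intensive/joint agency.

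**The concern.** The rule is all-or-nothing. If the number of controls is judged insufficient, the usual-care contrast is not reported with less precision or downgraded to an estimate. It is replaced, for both primary outcomes at once. What remains is the contrast that the article itself ranks as exploratory.

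The two primary outcomes also have very different requirements, 140 against 21 analysable per group, so a single undifferentiated rule cannot suit both. A control group well short of the NPI target can still be several times the size that the plan asks for on the GHQ-12. At stake is whether the study reports anything on its main question in a situation that the authors regard as realistic.

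**Working it through.** **Inputs (Sample size section).** NPI: difference 5.2, SD 13.7 (intervention) and 20.3 (control), within-subject correlation 0.5. GHQ-12: difference 2.2, SD 2.8 and 3.4, correlation 0.6. Satterthwaite t-test, one-sided 5%.

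**Change-score SD** = SD × √(2(1 − ρ)).
- NPI: √(2 × 0.5) = 1, so 13.7 and 20.3 are unchanged.
- GHQ-12: √(2 × 0.4) = √0.8 = 0.894, giving 2.504 and 3.041.

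**Formula.** SE = √(s₁²/n₁ + s₂²/n₂). Power comes from the noncentral t with Satterthwaite degrees of freedom and noncentrality difference/SE. The 95% half-width is t(0.975, df) × SE.

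**The plan's own figures reproduce.**
- NPI: 80% power needs 138 per group; 140 per group gives 80.5%; 140/0.80 = 175.
- GHQ-12: 21 per group gives 80.8%; 21/0.80 = 26.25, against at least 26 stated.

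**NPI with fewer analysable controls, against 140 in one model.** Example at 70 controls: SE = √(13.7²/140 + 20.3²/70) = √(1.341 + 5.887) = 2.688; df 101.4; half-width = 1.984 × 2.688 = 5.33.

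| Controls | SE | Power, one-sided | 95% half-width | Power, 1-to-1 matched |
|---|---|---|---|---|
| 140 | 2.07 | 80.5% | 4.1 | 80.5% |
| 100 | 2.34 | 72% | 4.6 | 68% |
| 70 | 2.69 | 61% | 5.3 | 55% |
| 60 | 2.87 | 56% | 5.7 | 50% |
| 50 | 3.10 | 51% | 6.2 | 44% |
| 26 | 4.15 | 34% | 8.5 | 28% |

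Controls carry the larger SD, so losing them is costly and extra case management participants recover little. Pooling both models (280) gives 76% at 100 controls and 59% at 60, a gain of 3 to 5 percentage points.

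**GHQ-12, against 140 in one model.**

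| Controls | Power, effect 2.2 | Power, 1-to-1 matched | Power, effect 1.1 (assumed) |
|---|---|---|---|
| 21 | 92% | 81% | 46% |
| 26 | 96% | 88% | 52% |
| 60 | over 99% | over 99% | 79% |
| 70 | over 99% | over 99% | 83% |

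The last column is unmatched.

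**The fallback contrast.** The article gives no effect or SD for it. Assuming SD 13.7 in both models and 140 per model, one-sided NPI power is 94% for a difference of 5.2, 48% for 2.6 and 20% for 1.3. Two active models may well differ from each other by less than either differs from usual care.

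**The case against.** Several points can be made for the plan, and some of them stand.

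- **The powers are crude.** The comparison is not randomised. Effect evaluation requires propensity scores for each model versus usual care, and the Discussion lists many confounders and possible regional clustering. With about 21 controls such a model is hardly estimable. The Discussion itself warns that low participation feeds confounding by indication. This stands: 92% is power for an unadjusted difference, and a reader should not infer that 21 controls would settle the caregiver question.
- **The NPI suffers.** A reader might infer that far fewer controls would still give useful NPI precision. The figures do not support that. At 70 controls the 95% half-width (5.3) already exceeds the target difference of 5.2, and at GHQ-sized numbers the interval says little. Two-sided NPI power, relevant because the article promises 95% intervals, is 60% at 100 controls and 43% at 60.
- **The GHQ-12 effect is large and comes from a six-month study**, while follow-up here is two years. This stands, hence the 1.1 column.
- **Enrolled controls.** A reader might infer that controls already enrolled would be thrown away. The article does not say so; it says only which groups will be compared.
- **No threshold for sufficient recruitment.** The full protocol, which is not shown, may define it, so this is not counted as a defect.
- **The comparison between models is planned anyway**, and an exploratory contrast needs no power statement. True, but that does not justify letting it stand in for the first hypothesis.

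None of these points is a reason to report no usual-care comparison. They limit how strong the retained comparison would be.

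**Conclusion.** The concern holds in a limited form. The article states a rule which, wherever its threshold lies, leaves the first hypothesis untested on both primary outcomes and puts an unsized exploratory contrast in its place. This is a consequence of what is written, not a missing detail.

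The rule is unnecessary for the GHQ-12 over a wide range of shortfalls: 60 controls, fewer than half the planned 140, keep power above 99% at the assumed effect and 79% at half of it. For the NPI it is unnecessary only for a moderate shortfall, roughly 70 to 100 analysable controls. At about 50 and below, the NPI result is a weak estimate.

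All figures rest on the plan's SDs, correlations and effects, a one-sided 5% level and an unadjusted comparison. Propensity adjustment and clustering can be expected to lower them by an amount that the article does not allow one to calculate.

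**What to change.** Replace the contingency sentence with a rule along these lines:

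- The usual-care comparison is kept and reported for both primary outcomes whatever number of controls is recruited. It uses all of them, with unequal group sizes, the planned confounder adjustment as far as the number of controls allows, and the achieved confidence interval.
- If controls fall short of the NPI requirement, the NPI comparison is presented as an estimate. The GHQ-12 comparison is kept as planned as long as its own required number is met.
- Linkage versus intensive/joint agency stays exploratory in every case.

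Pooling the two models against usual care can be a supplementary analysis. It need not become the primary contrast: it adds only 3 to 5 points of NPI power at 60 to 100 controls, merges models that the study sets out to distinguish, and would make the primary contrast depend on achieved recruitment.

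The cost is a short change of text, no additional data collection, and acceptance that a wider and less favourable NPI interval may have to be reported.
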